## Abstract

**Background:**

Stillbirth and neonatal death are devastating pregnancy outcomes with long-lasting psychosocial consequences for parents and families, and wide-ranging economic impacts on health systems and society. It is essential that parents and families have access to appropriate support, yet services are often limited. Internet-based programs may provide another option of psychosocial support for parents following the death of a baby. We aim to evaluate the efficacy and acceptability of a self-guided internet-based perinatal bereavement support program “Living with Loss” (LWL) in reducing psychological distress and improving the wellbeing of parents following stillbirth or neonatal death.

**Methods:**

This trial is a two-arm parallel group randomized controlled trial comparing the intervention arm (LWL) with a care as usual control arm (CAU). We anticipate recruiting 150 women and men across Australia who have experienced a stillbirth or neonatal death in the past 2 years. Participants randomized to the LWL group will receive the six-module internet-based program over 8 weeks including automated email notifications and reminders. Baseline, post-intervention, and 3-month follow-up assessments will be conducted to assess primary and secondary outcomes for both arms. The primary outcome will be the change in Kessler Psychological Distress Scale (K10) scores from baseline to 3-month follow-up. Secondary outcomes include perinatal grief, anxiety, depression, quality of life, program satisfaction and acceptability, and cost-effectiveness. Analysis will use intention-to-treat linear mixed models to examine psychological distress symptom scores at 3-month follow-up. Subgroup analyses by severity of symptoms at baseline will be undertaken.

**Discussion:**

The LWL program aims to provide an evidence-based accessible and flexible support option for bereaved parents following stillbirth or neonatal death. This may be particularly useful for parents and healthcare professionals residing in rural regions where services and supports are limited. This RCT seeks to provide evidence of the efficacy, acceptability, and cost-effectiveness of the LWL program and contribute to our understanding of the role digital services may play in addressing the gap in the availability of specific bereavement support resources for parents following the death of a baby, particularly for men.

**Trial registration:**

Australian New Zealand Clinical Trials Registry, ACTRN12621000631808. Registered prospectively on 27 May 2021.

**Supplementary Information:**

The online version contains supplementary material available at 10.1186/s13063-022-06363-0.

Composition, roles and responsibilities	**Coordinating centre and data management team:** The Centre of Research Excellence in Stillbirth (Stillbirth CRE), Mater Research Institute-University of Queensland based in Brisbane Queensland Australia is responsible for the overarching conduct and coordination of this study. The coordinating research team ([name]) are based at the Stillbirth CRE and are responsible for the day-to-day conduct of the study including participant monitoring and data management. **Steering committee:** An advisory group has been established to oversee and review conduct of this study with meetings scheduled every three months, and monthly updates provided via email correspondence. This steering group includes bereaved parents, health care professionals, clinicians, researchers, and parent support and advocacy organisations. The role of this group is to provide specialist knowledge of perinatal bereavement care and mental health, lived experience of perinatal loss, and trial support and advice throughout all stages of the study, including development, evaluation, and dissemination of findings.

## Background

The death of a baby during pregnancy or soon after birth is a devastating outcome for families and remains a public health priority in Australia and internationally. In Australia, eight stillbirths (defined as the birth of a baby without signs of life after 20 weeks gestation) and neonatal deaths (defined as a baby that dies after birth within 28 days) occur each day, with little change in rates over the past 30 years [1–4]. The long-lasting psychological and emotional consequences for parents, families, and care providers, and the wide-ranging impacts on health systems and society are now well-recognized [5, 6]. Bereaved parents report intense sadness, anxiety, guilt, anger, and experiences of stigma, shame, and disenfranchisement of their grief [7, 8]. Perinatal bereavement is also associated with increased risk for persistent psychological difficulties including posttraumatic stress disorder (PTSD), major depressive disorder (MDD), and prolonged grief disorder (PGD) [6, 9].

The provision of respectful and supportive perinatal bereavement care to parents and families around stillbirth and neonatal death is a major contributor to their immediate and long-term wellbeing [10]. Community-based settings are vital to providing ongoing support to parents following hospital discharge, but support received is often inadequate [4, 11, 12]. The Lancet Ending Preventable Stillbirth Series highlighted the unmet needs of bereaved parents following hospital discharge with 31% of women describing their post-hospital care after stillbirth as poor [4, 11]. Critical gaps exist in the transition from hospital-to-home and in providing ongoing bereavement support for families following a baby’s death [4, 11, 12]. Health professionals report barriers to the effective provision of perinatal bereavement care, including insufficient training and experience in bereavement care, a lack of clear care pathways, and limited availability of support systems and structures for parents [5].

Access to a range of bereavement support options is often recommended to meet the varying needs of individuals [13]. Yet little is known about the acceptability and effectiveness of different types of bereavement support, and whether this differs between parents [14]. For men, in particular, the psychological and emotional impact of stillbirth and neonatal death has been under-explored in comparison to women [15–17]. A systematic review by Obst and colleagues highlighted the importance of tailored perinatal bereavement support resources that validated men’s experiences of grief following a baby’s death [18].

Over the past two decades, the digital delivery of mental health services via the Internet has been increasingly used in Australia to reduce barriers to care provision and increase availability and accessibility of services. Internet-based interventions, predominately based on cognitive behavioral therapy (referred to as “iCBT”), are now well-established for the treatment of a range of mental health disorders including anxiety and depression in children and adolescent [19], and general adult [20], and perinatal populations [21–23]. Digital mental health tools and services already form part of routine care in many countries, often operating within a stepped-care approach as a stand-alone service (i.e., low-intensity support) or in conjunction with face-to-face care services (i.e., high-intensity support) [24, 25]. Low-intensity internet-based programs, with or without therapist guidance or coaching, can provide users with a self-managed flexible support option that can be accessible at any convenient time or place (e.g., at home) and can allow for a greater degree of anonymity and privacy [20, 25]. This is possibly important in the context of perinatal bereavement given the death of a baby during pregnancy often receives little community acknowledgement. Many parents may be reluctant to seek help and disclose emotional difficulties to others following a loss that is often misunderstood and subject to social stigma [26]. Telehealth is now in widespread use in maternal healthcare, and many parents would already be likely to have encountered some form of digital service delivery during their care, this potentially adding to the acceptability and familiarity of parents with a digital mode of bereavement support [27].

Internet-based programs for people experiencing bereavement appear promising yet evidence is limited. A systematic review and meta-analysis of internet-based interventions for grief after bereavement [28] found seven studies which demonstrated moderate effects for symptoms of grief, depression, and posttraumatic stress symptoms, and high user satisfaction and intervention quality. To our knowledge, only one RCT has evaluated an internet-based intervention for parents after pregnancy loss. Kersting and colleagues evaluated a 5-week therapist-guided program (delivered in German language) for parents who had experienced miscarriage, termination of pregnancy for medical reasons, or stillbirth [29]. The program was based on CBT and focused on exposure (self-confrontation), cognitive restructuring, and social sharing and included structured personalized writing assignments that were reviewed by an internet-based therapist. Parents (92% were female, mean age of 34 years) that completed the intervention (*n* = 115) demonstrated significantly reduced symptoms of grief, posttraumatic stress, and depression at post-intervention compared with the wait-list control group (*n* = 113). In addition to low attrition rates (14%), significant improvements in symptoms were maintained at 3-month and 12-month follow-ups.

Generally, internet-based interventions for bereavement appear to be most effective for people experiencing significant loss-related distress and complicated grief responses; users that are self-referred; and when the intervention includes some elements of CBT [30, 31]. Further research is needed to determine whether digital support options, including internet-based interventions, can address the gap in the availability of specific bereavement support for parents following the death of a baby, especially men. Future research should also explore the impact of internet-based interventions on perceived psychological or personal growth outcomes after perinatal bereavement, such as posttraumatic growth, resilience, and coping [32–34]. Evaluation of digital support services is particularly important given the COVID-19 pandemic has resulted in many healthcare services and support organizations rapidly pivoting from face-to-face delivery to digital services.

The *NHMRC Centre of Research Excellence in Stillbirth* (Stillbirth CRE) have led the development of a parent-centered internet-based program to improve the emotional wellbeing of parents following stillbirth or neonatal death and expand the availability and accessibility of evidence-based bereavement care options in Australia for parents and healthcare professionals. The aim of this trial is to conduct a RCT to evaluate the efficacy and acceptability of the internet-based Living with Loss (LWL) perinatal bereavement program, compared to standard usual care. We hypothesize that the LWL program will:Reduce symptoms of psychological distress compared with usual care.Reduce grief intensity, anxiety, depression, decisional regret, and improve quality of life outcomes compared to usual care.Be perceived as helpful, with participants reporting high levels of program satisfaction including usability, credibility and quality; and low attrition rates.Be cost-effective compared with usual care.

## Methods/design

### Design and setting

The LWL trial is a two-arm, parallel group, superiority trial comparing the intervention arm (LWL group) with a care as usual control arm (CAU group). This trial will be conducted and reported according to the CONSORT-EHEALTH [35] and Standard Protocol Items: Recommendations for Interventional Trials (SPIRIT) 2013 statement ([36]; see Additional file 1). This 21-week trial includes three assessment timepoints: (1) baseline; (2) post-intervention; and (3) 3-month follow-up. This trial has been approved by the Mater Misericordiae Ltd Human Research Ethics Committee (HREC/MML/70343) and registered with the Australian New Zealand Clinical Trials Registry (ACTRN12621000631808). This trial is being conducted by the Stillbirth CRE, Mater Research Institute-University of Queensland (MRI-UQ) in Brisbane, Queensland Australia. The Stillbirth CRE leads a national program of research and implementation to reduce the number of preventable stillbirths and neonatal deaths in Australia and internationally, and to improve care for women, families, and the community when the death of a baby does occur. This trial is being conducted online with no face-to-face contact with participants. All trial procedures and outcome assessments are completed online via the LWL course delivery system.

### Development of an internet-based perinatal bereavement program

The LWL program focuses on the psychosocial needs of parents and aims to provide a range of practical strategies in self-care and emotional management. Program content was developed by a team of clinicians, researchers, parent support and advocacy organizations, and bereaved parents who collectively provided specialist knowledge of perinatal bereavement care and mental health, and lived experience of perinatal loss. Development was guided by the principles of co-design with emphasis placed on engagement with end-users and the views of lay people [37]. Qualitative semi-structured interviews were conducted with parents and healthcare professionals in community settings. Interviews explored barriers and enablers to bereavement care support options, and the needs and preferences of parents and healthcare professionals for an internet-based perinatal bereavement program.

The LWL program consists of six modules covering a broad range of topics that bereaved parents and healthcare professionals have highlighted as important (see Table 1) [11, 38]. In the absence of a Core Outcome Set (COS) for stillbirth and neonatal death, program topics were mapped to the COS identified for coping and wellbeing in bereavement for adults in palliative care settings (see Table 1) [13]. Program content is based on a range of cognitive and behavioral approaches to bereavement including strategies from cognitive behavioral therapy (CBT), acceptance and commitment therapy (ACT), mindfulness, and compassion-focused therapy. In line with the current evidence base for perinatal bereavement, program content focused on normalizing and validating the individual grief experience and coping processes and avoided pathologizing grief. Content was written from the perspective of the dual-process model of coping with bereavement which suggests individuals oscillate between loss-oriented and restoration-oriented coping and highlights the various cognitive, behavioral, emotional, relational, and motivational impacts of bereavement [39].

**Table 1 Tab1:** Components of the *Living with Loss* online perinatal bereavement program

Module	Topic	Outcome^**a**^
**Module 1: Understanding grief**	• Understanding grief experience • Managing and coping with behavioral and physical grief reactions (e.g., tension) • Understanding the difference between grief and anxiety, depression, and trauma; including referral pathways for support • Activity planning including self-care and sleep quality • Mindfulness exercise and targeted relaxation and stress reduction techniques	Acceptance of grief as normal; increased understanding of the experiences of challenging mental and emotional states (e.g., feelings of tension, panic, distress or worry); improved daily functioning and increased participation in regular activities.
**Module 2: Managing Intense Feelings**	• Understanding the emotional impact of grief and loss • Identifying and accepting intense feelings such as anger, guilt, blame, regret; moving from self-criticism to self-compassion • Exploring creative practices such as self-compassion through writing • Mindfulness exercise including elements of acceptance and commitment therapy (ACT)	Improved coping with negative and challenging emotional states and overwhelming feelings of grief.
**Module 3: Balancing Thoughts**	• Understanding the cognitive impact of grief and loss; how thoughts, feelings, and actions interact • Identifying and reframing unhelpful thoughts through a thought monitoring strategy • Mindfulness meditation and grounding activity to reduce anxiety	Improved coping with negative and challenging mental states and overwhelming thoughts of grief.
**Module 4: Facing Hard Situations and Conversations**	• Understanding the social and functional context of grief • Identifying and planning for difficult situations and times ahead (e.g., memories, anniversaries) using structured problem-solving and planners (e.g., return to work) • Managing worried and repetitive thoughts through scheduled worry time and self-compassion breaks • Mindfulness meditation and self-compassion-focused exercise	Practical strategies for social and occupational reintegration; increased participation in work and social activities; confidence accessing support when needed.
**Module 5: Strengthening Relationships and Communication**	• Understanding the impact of grief on relationships including differences in grief between partners and family members • Identifying types of support (practical, emotional) including strategies for how to ask and access help and importance of connectedness with others • Strategies to communicate and set helpful boundaries with others • Mindfulness meditation and self-compassion-focused exercise	Effective strategies for enhancing communication and connectedness with others; improved relationships and social functioning.
**Module 6: The Future**	• Understanding how grief can change over time • Exploring ways to find meaning in grief and renewed sense of purpose in life • Planning for the future and accessing appropriate emotional support when needed • Mindfulness meditation and self-compassion-focused exercise	Finding meaning in grief over the longer term; finding balance between grief and life going forwards; sense of meaning and purpose in life.

^a^Mapped to COS for coping and wellbeing in bereavement [13]

The LWL program is delivered via a custom-built online learning management system and viewed by parents on a computer, tablet, or smartphone with an internet connection. To encourage engagement with the program, each module consists of three sections. First, a short series of illustrated parent stories is viewed which delivers content through dialogue between several characters. This targeted style of information delivery has been shown to be acceptable in other digital mental health programs for perinatal women [21, 22]. This approach allows for a range of character experiences and engagement with different bereavement support services (e.g., one-on-one counselling; community-based support group) to be included which aims to normalize and validate varied individual experiences. Summary information is then displayed on-screen over several brief pages to provide parents with more information addressing key topics and strategies. This information is consolidated via 1–2 exercises or activities which can be completed on-screen and then downloaded and/or printed for later reflection and use. Each module concludes with a grounding mindfulness or compassion-focused meditation. Throughout each module, information is provided at several points to link parents with further support options if needed (e.g., peer and mental health telephone support). A library of resources accessible throughout the program also provides parents with additional information (e.g., websites, books, reading material).

Participants are required to complete the introductory module (Module 1). Once this is accessed, all other modules will become available. Apart from this requirement, the program is designed to be flexible so that participants can complete modules in their preferred order and time period. However, participants are encouraged to complete Module 6 last, as this module focuses on planning for the long term and acts as a conclusion to the overall program, although this is not enforced.

### Participants and recruitment

An opportunity sample of self-selecting participants will be recruited via a snowball sampling strategy. Parents and healthcare professionals will be notified of this trial through online and social media advertising, flyers at local maternity services (e.g., Mater Mothers’ Hospital, Brisbane, Australia), and by word of mouth (e.g., healthcare professionals; parent support organizations). All parents interested in participating are directed to the LWL website to review participant information and express interest. This trial aims to recruit at least 75 participants in each study arm (total *N* = 150) which allows for an anticipated dropout rate of 25% (see Statistical methods). Participants will be recruited over a 12-month period.

#### Inclusion criteria

This study will recruit parents who have experienced a stillbirth (defined as a baby that dies before birth and after 20 weeks’ gestation including termination of pregnancy for medical reasons) or neonatal death (defined as a baby that dies after birth and within 28 days) in the past 2 years and more than 8 weeks ago. Additional inclusion criteria include: aged 18 years and older; currently residing in Australia; access to a computer with Internet connection; written and oral fluency in English language; willingness to provide personal contact details (including emergency contact); and willingness to provide informed consent online.

#### Exclusion criteria

The exclusion criteria are as follows: parents in a current pregnancy; those who have experienced an early pregnancy loss (i.e., before 20 weeks’ gestation); stillbirth or neonatal death less than eight weeks ago; or a diagnosis of psychosis, bipolar disorder, or schizophrenia within the last 2 years. Individuals who are experiencing severe symptoms of psychological distress, depression, and/or suicidal ideation at enrolment will also be excluded.

### Procedures

#### Online screening and enrolment

The enrolment and study procedure is outlined in Fig. 1. To enrol, applicants are directed to the LWL website where participant information is provided. To register, applicants are required to read the participant information on-screen, answer eligibility questions based on inclusion and exclusion criteria, and provide online informed consent to participate (by selecting the response option: “Yes, I would like to participate in this research study” on-screen). Applicants that do not meet inclusion criteria are notified on-screen that they are not eligible for this trial and provided with information on parent support organizations. Parents that do not wish to provide consent to participate are asked to close their web browser. Applicants are then asked to complete their personal account details (i.e., personal contact details; emergency contact details; demographics; password for account). All participant account information is confidential and accessible only to the research team based at the coordinating center via the LWL course delivery system.

**Fig. 1 Fig1:**
[figure not shown]
Participant flowchart illustrating enrolment and study procedure

During enrolment, applicants are also required to complete two baseline questionnaires which act as a screener for severe symptoms of the distress, depression, and/or suicidal ideation exclusion criteria; indicated by a total score of 30 or greater on the Kessler Psychological Distress Scale (K10) [40]; and/or a total score of 14 or greater on the Edinburgh Postnatal Depression Scale (EPDS) [41]; and/or a score of 1, 2, or 3 on Item 10 of the EPDS, respectively. There are two outcomes following this screening questionnaire:Applicants that screen negative (do not meet this exclusion criteria) will be eligible to participate and will proceed to the first assessment timepoint to complete baseline questionnaires prior to randomization.Applicants that screen positive will have their application paused and be notified on-screen and via automated email that the trial clinician will be in contact via telephone to finish their application. During this enrolment interview, the trial clinician will conduct a risk assessment and use clinical judgment to determine eligibility. This is in line with most efficacy studies of digital mental health interventions (i.e., considered low-intensity support) which exclude individuals that are experiencing severe depressive symptoms and are at risk of suicide, and refer to face-to-face services (i.e., high-intensity support [42];. In addition to understanding the applicant’s individual circumstances and support network, this interview will take into consideration that this is an RCT (individuals can be allocated to the control arm) evaluating a self-guided intervention (no therapist support or coaching; content does not address severe depression or suicidal ideation) and delivered solely via the Internet (with no direct participant contact; participants can reside anywhere in Australia). Following the interview, eligible applicants will be asked to return to the LWL website to continue their application. For applicants that are not eligible, referral information for support services will be discussed and provided via email.

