#### Safety monitoring

Two primary strategies are in place to monitor participants and ensure their safety throughout the trial. Participant progress will be monitored by the trial clinician to identify elevated distress or risk of harm. The trial clinician [name] is a registered psychologist in Australia with clinical experience in managing perinatal mental health difficulties and diagnoses. Both the participant and the trial clinician will receive automated notification emails if severe symptoms of distress (i.e., total score ≥30 on the K10), depression (i.e., total score ≥13 on the EPDS), or thoughts of self-harm (i.e., item 10 on the EPDS, item 8 on the Perinatal Grief Scale-Short Form (PGS-SF) [43], or item 16 on the Assessment of Quality of Life (AQoL-8D) [44] are indicated at any of the primary timepoints. This notification email will encourage participants to seek support from their support network (e.g., partner, family member) and health professional (e.g., GP/Family Doctor), and if feeling unsafe, to contact emergency or crisis support services. Participants will be contacted by the trial clinician within 72 h via telephone to conduct a risk assessment and determine whether the participant is still eligible to continue in the study, and will be provided assistance to find appropriate support and clinical care if required.

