### Outcomes

Primary and secondary outcomes will be collected at three primary timepoints: baseline, post-intervention, and 3-month follow-up (see Table 2).

**Table 2 Tab2:** Schedule of outcome measures and timepoints

	Baseline	Active study period^a^		Post-intervention	3-month follow-up
		Weekly	End of each module		

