***Secondary outcomes***					
PGS	x			x	x
GAD-7	x			x	x
EPDS	x*			x	x
BGQ	x				
RSA	x				
DRS	x			x	x
Support use	x			x	x
AQoL-8D	x			x	x
HSUS	x			x	x
***Acceptability outcomes***^a^					
CEQ			x^b^		
MSS			x		
PSQ				x	

*K10* Kessler Psychological Distress Scale, *PGS* Perinatal Grief Scale, *GAD-7* Generalized Anxiety Disorder Scale, *EPDS* Edinburgh Postnatal Depression Scale, *BGQ* Brief Grief Questionnaire, *RSA* Resilience Scale for Adults, *DRS* Decisional Regret Scale, *CEQ* Credibility and Expectancy Questionnaire, *MS* Module Satisfaction Scale, *PSQ* Program Satisfaction Questionnaire, *AQoL-8D* Assessment of Quality of Life, *HSUS* Health Service Utilization Scale

*Completed during enrolment screening questionnaire; ^a^LWL group only; ^b^end of Module 1 only

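### Two EPDS cut-offs for severe depression (14 at screening, 13 in monitoring) apply to the same baseline form, so a score of 13 is cleared for randomisation and can then reopen eligibility after allocation

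*Protocol article*

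**What the plan says.** All references are to the protocol article.

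- **Exclusion criteria:** "Individuals who are experiencing severe symptoms of psychological distress, depression, and/or suicidal ideation at enrolment will also be excluded". No cut-offs are given here.
- **Online screening and enrolment** (text after Fig. 1) gives the scores that indicate this exclusion: "a total score of 30 or greater on the Kessler Psychological Distress Scale (K10"), and/or "a total score of 14 or greater on the Edinburgh Postnatal Depression Scale (EPDS"), and/or a response of 1, 2 or 3 on EPDS item 10. Applicants who screen negative are eligible and go on to the baseline questionnaires. For those who screen positive, "the trial clinician will conduct a risk assessment and use clinical judgment to determine eligibility".
- **Randomization and allocation procedures:** the system randomises as soon as the baseline questionnaires are finished. Allocation is then open to participants and research personnel. Outcome data stop for anyone who withdraws or drops out.
- **Safety monitoring:** an alert goes out if K10 is 30 or more, for "depression (i.e., total score ≥13 on the EPDS"), or for self-harm items (EPDS item 10, PGS-SF item 8, AQoL-8D item 16), when these "are indicated at any of the primary timepoints". The trial clinician then telephones within 72 hours, assesses risk and decides whether the person may remain in the trial.
- **Outcomes:** "Primary and secondary outcomes will be collected at three primary timepoints: baseline, post-intervention, and 3-month follow-up". In Table 2 the baseline K10 and EPDS carry an asterisk, explained as "Completed during enrolment screening questionnaire".

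**The concern.** Severe depression has two values, and both are applied to one administration of one questionnaire. A score of 13 is not severe when eligibility is decided before randomisation, and is severe when the monitoring rule reads the same form. The monitoring rule does more than offer support: it asks again whether the person is eligible.

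At stake is the timing of that second decision. Randomisation is automatic, so the call comes after allocation and may be made by someone who knows the arm. If the person leaves the trial as a result, no further outcome data are collected. The missing data would then be linked to baseline severity, and could be linked to arm.

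A secondary point is that Exclusion criteria reads as a flat exclusion, while Online screening and enrolment lets the clinician admit people who screen positive.

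**Working it through.** No sample size, power or alpha figure is involved, so there is nothing in the plan to reproduce. The check compares the two rules on the scores they share.

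**Step 1: is it the same form?** Monitoring applies at every primary timepoint, and Outcomes names baseline as one of them. Table 2 shows one baseline EPDS and one baseline K10, both marked as taken at the enrolment screen. Both rules therefore read the same scores.

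**Step 2: the rules.**

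- Screening positive: K10 ≥ 30, or EPDS ≥ 14, or item 10 ≥ 1.
- Monitoring positive on the shared scores: K10 ≥ 30, or EPDS ≥ 13, or item 10 endorsed. Safety monitoring gives no score for item 10; I take endorsed to mean 1 or more.

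**Step 3: where they differ.** K10 of 30 or more, or item 10 of 1 or more, makes both rules positive whatever the EPDS total. Only K10 below 30 with item 10 = 0 is left:

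| EPDS total (K10 = 29, item 10 = 0) | Screening | Monitoring | Agree? |
|---|---|---|---|
| 11 | negative | negative | yes |
| 12 | negative | negative | yes |
| 13 | negative | positive | **no** |
| 14 | positive | positive | yes |

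Over the full grid of K10 29 or 30, EPDS 11 to 14 and item 10 of 0 or 1 (2 × 4 × 2 = 16 combinations), this is the only disagreement.

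**Step 4: the path of that applicant.** The screen is negative, so the applicant is eligible, completes the baseline questionnaires and is randomised automatically. The arm is shown. The baseline EPDS of 13 meets the alert rule, and a call within 72 hours decides whether the person continues.

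**Step 5: screen-positive applicants whom the clinician admits.** Each has K10 ≥ 30, EPDS ≥ 14 or item 10 ≥ 1, so each also meets the monitoring rule on the same form. Eligibility was settled at the enrolment interview, and the text reopens it after allocation on the same scores. This would happen even with a single EPDS cut-off.

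**Step 6: what is not in conflict.** The K10 cut-off is 30 in both sections. The EPDS value of 12 under Secondary outcomes is labelled as possible depression, not severe. PGS-SF item 8 and AQoL-8D item 16 are not screening items, so a baseline alert on either is new information.

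**The case against.** **Screening comes before baseline.** The enrolment text has screen-negative applicants moving on to the first assessment timepoint, and it speaks of applicants where Safety monitoring speaks of participants. On that reading the screening form falls outside the monitoring rule, and baseline alerts serve only what is newly collected. Fig. 1, which might settle the order, is not shown. This reading does not fit Outcomes and Table 2, which count the screening K10 and EPDS as the baseline measurements. At best the text supports both readings.

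**Two cut-offs may be deliberate.** A more sensitive alert than screen is conceivable, but the protocol does not say so, and both values are described as severe. Nor would it explain reconsidering eligibility on a form already judged.

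**Exclusion versus discretion is ordinary practice.** Much of this stands. The enrolment text can fairly be read as putting the exclusion criterion into operation: a score triggers an interview and the clinician decides. A reader might infer that the enrolled population is undefined. It is not: it consists of screen-negative applicants plus screen-positive applicants whom the clinician admits. The two sections still need matching words.

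**The eligibility review is not specific to the EPDS mismatch.** This also stands. The review applies at every primary timepoint and would remain if the cut-offs were aligned, so the fix has to address timing as well as the number. Review at later timepoints, on new scores, is monitoring as described and is not criticised here.

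**Leaving the trial is not exclusion from analysis.** Data analyses plans intention-to-treat mixed models, so data already collected would stay in. But someone removed in the first days would contribute only baseline values.

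**Conclusion.** The contradiction is in the text. One baseline EPDS form is subject to two cut-offs for severe depression, and the second can reopen eligibility after allocation. It should be corrected because the rule governs both safety and eligibility, and correction is cheap.

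Its reach is narrow. The cut-offs disagree only at EPDS 13 with K10 below 30 and item 10 = 0. Screen-positive applicants whom the clinician admits are a second group whose eligibility is reopened on scores already judged. The protocol gives the number in neither group; it is probably small.

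Two stronger readings are not supported. A reader might infer that a threshold with two values cannot be audited, but each value belongs to its own procedure and can be checked against recorded scores. A reader might also express each removal as a share of the participants left after dropout (150 × 0.75 = 112.5; 1/112 = 0.9%). That denominator already carries the 25% dropout allowance, so the loss is counted twice; against those randomised it is 1/150 = 0.7%. No effect on power, type I error or the primary estimate has been shown.

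The conclusion assumes that the Table 2 footnote means what it says, and that someone found ineligible at the call is handled like a withdrawal. The protocol does not state the latter.

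**What to change.** Reconcile Exclusion criteria, Online screening and enrolment, and Safety monitoring:

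1. Use one EPDS definition of severe symptoms, or state that two are intended and why. The clinical team must choose; none is proposed here.
2. State that trial eligibility based on the screening K10 and EPDS is settled before allocation, so that a baseline alert on those scores does not reopen it. Safety follow-up after an alert is unaffected.
3. Word the exclusion criterion to match the clinician-decision pathway.

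The cost is protocol wording, an ethics notification and, if a cut-off changes, one setting in the course delivery system. Recruitment is under way (62 randomised by 1 February 2022), so the number already affected can be counted from recorded screening scores.
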